### Study sample characteristics

Screening and baseline interviews began in Oct, 2012, and are ongoing. We here present the baseline characteristics of the first 37 subjects who have been enrolled and initiated on-site anti-TB and DM treatment: Of these, 8 were randomized to the VA arm, 10 to VD arm, 9 to VAD arm and 10 to the control arm (Figure 1).

**Figure 1 F1:**
[figure not shown]
Flow chart of study recruitment and enrollment.

The sample is 91.9% male, 97.3% ethnic Han, with a mean age of 52 (Table 1). 83.8% subjects have education level of senior high school or lower, 75.7% married, 48.6% employed. 75.7% subjects’ BMI were normal(18.5~24.99)with one patient being severe wasting, 5 patients being mild wasting and 3 patients being overweight.

**Table 1 T1:** Baseline characteristics of study sample (n =37)

**Sociodemograpic**	
Age, mean (sd)	52 (12.0)
Gender, n (%)	
Male	34 (91.9)
Female	3 (8.1)
Race, n (%)	
Han	36 (97.3)
Other	1(2.7)
Education, n (%)	
Senior high school or lower	31 (83.8)
Junior College and college	6 (16.2)
Marriage Status, n (%)	
Married	28 (75.7)
Widowed/divorced/single	9 (24.3)
Employed, n (%)^a^	
Employed	18 (48.6)
Retired/Unable to work/unemployed/other	16 (43.2)
**PTB-related Admission Symptoms**, n (%)	
Cough+	35 (94.6)
Cough-	2 (5.4)
Expectoration+	33 (89.2)
Expectoration-	4 (10.8)
Hemoptysis+	11 (29.7)
Hemoptysis-	26 (70.3)
Fever+	18 (48.6)
Fever-	19(51.4)
Weak+	28(75.7)
Weak-	9(24.3)
Night sweat+	19(51.4)
Night sweat-	18(48.6)
Thoracalgia+	8(21.6)
Thoracalgia-	29(78.4)
Chest stufly+	20(54.1)
Chest stufly-	17(45.9)
**PTB-related CT pathology**, n (%)	
Pulmonary cavity +	27(73)
Pulmonary cavity –	10(27)
Pulmonary infiltration+	1(2.7)
Pulmonary infiltration-	36(97.3)
**Admission Biochemical index**	
FPG, mmol/L(mean,sd)	12.19, 3.30
LDL-C, mmol/L (mean,sd)	2.42, 0.63
TC, mmol/L (M, interquartile range)	4.29, 0.85
TG, mmol/L (M, interquartile range)	1.66, 0.79
HDL-C, mmol/L (mean,sd)	1.21, 0.29
**BMI**^**b**^, n (%)	
<16	1(2.7)
16~16.9	0 (0)
17~18.4	5(13.5)
18.5~24.99	28(75.5)
25~29.99	3(8.1)
>30	0(0)

^a^ missing data.

^b^<16: severe wasting; 16~16.9: moderate wasting; 17~18.4: mild wasting; 18.5~24.99: normal; 25~29.99: overweight; ≥ 30: obesity.

At baseline, 94.6% of the sample had cough, 89.2% had expectoration, 29.7% had hemoptysis, 48.6% had fever, 75.7% had weak, 51.4% had night sweat, 21.6% had thoracalgia, 54.1% had chest stufly. As to pulmonary pathology inspected by CT, 73% of the sample had pulmonary cavity, 2.7% had infiltration. Admission biochemical examine showed that the mean fast plasma glucose concentration was 12.19 mmol/L, mean LDL-C level was 2.42 mmol/L, median TC concentration was 4.29 mmol/L, median TG concentration was 1.66 mmol/L, mean HDL-C level was 1.21 mmol/L.

Our intervention is feasible and can be implemented in a busy clinical setting. Staff at the four clinics worked collaboratively with the study team, and to date 37 participants have been enrolled from the four clinics. Health care providers communicate well with the medical director and research assistants, and nurses at each clinic record daily events on study calendars. To date, a total of 51 subjects have been screened (Figure 1).

The VA/D program is acceptable to our patients. To date, 88% of all patients who were eligible for receiving VA/D supplementation and met study inclusion and exclusion criteria have chosen to participate. No participants have refused their randomization.

The core components of our VA/D program do not require additional staff over existing clinic operating models. We will provide subsidies for medical providers, nurses, or support group facilitators on support of the Natural Science Foundation of China (NSFC) and Danone Nutrition and Education fund. We pay the VA and VD supplements used for the study.

## Discussion

To our knowledge, this study represents the first randomized controlled trial of a directly observed VA/D supplementation program in active pulmonary tuberculosis patients with diabetes that focused on the contribution of anti-TB and DM treatment effect and the possible mechanisms.

Tuberculosis and diabetes interact with each other, which might make clinical treatment become more difficult than the single disease of pulmonary tuberculosis or diabetes. As diabetes alters immunity to tuberculosis, longer times to culture conversion with treatment, and a higher rate of relapse might result. Treatment failure and death are more frequent in diabetic patients than patients with PTB alone. Alisjahbana reported that in patients with high adherence to treatment, 6-month sputum cultures were positive in 22.2% of patients with diabetes mellitus and in 6.9% of controls and these differences remained after adjustment for age, sex, body mass index, and other factors [15]. In a case–control study [16] treatment failure or death was seen in 41% of the patients with tuberculosis and diabetes mellitus, but in only 13% of those with tuberculosis alone. A recent study by Wang and colleagues [17] discovered that 1-year all-cause mortality was 17.6% in diabetic PTB patients versus 7.7% in non-diabetic controls, and death specifically attributable to pulmonary tuberculosis was significantly more common in diabetic patients (12.2% vs 4.2%).

The most important effector cells for containment of tuberculosis are phagocytes, monocytes and lymphocytes. Diabetes is known to affect chemotaxis, phagocytosis, activation, and antigen presentation by phagocytes in response to M tuberculosis. Vitamin A is an essential micronutrient for a variety of physiological processes, such as tissue differentiation, immunity, and vision. Also, the impacts of VA and retinoids on energy metabolism in animals and humans have been demonstrated in some basic and clinical investigations [18]. Also, it has been proposed recently that vitamin D play a critical role in immunity, respiratory health and insulin resistance. Vitamin A, its metabolites and vitamin D directly inhibit mycobacterial growth in culture [19].

A recent randomized trial of vitamin A and Zinc supplementation focused on the effect on treatment outcomes in TB patients and found that supplementation with vitamin A and zinc did not affect treatment outcomes in participants with pulmonary tuberculosis at 8 wk [20]. An important difference between this trial and our study is that single dose of 200,000 IU retinyl palmitate was used in the reported trial, while daily supplementation of 2000 IU retinol is being supplemented in our study. Also, vitamin A and Zinc supplementation on serum fasting blood sugar, insulin, apoprotein B and A-1 in patients with type I diabetes has been carried out [21], and found that combined zinc and vitamin A supplementation can improve serum apoprotein A-I, apoprotein B and the apoprotein B/apoprotein A-I ratio in patients with type I diabetes.

Some randomized controlled studies have focused on effect of vitamin D on glucose indices and vascular markers in type 2 diabetes[22,23], which found that Vitamin D supplementation attenuated the increase in glycemia, and increased insulin secretion, improved systolic blood pressure and B-type natriuretic peptide levels. Mitri et al. [14] implemented a 2-by-2 factorial-designed, double-masked, placebo-controlled trial and discovered that cholecalciferol (2000 IU once daily) supplementation for 16 wk can improved β cell function and had a marginal effect on attenuating the rise in Hb A(1c) in adults at risk of type 2 diabetes.

Vitamin D has been shown to be involved in the host immune response toward Mycobacterium tuberculosis. Recently several VD supplementation trials to active TB patients are available. Administration of four doses of 2.5 mg vitamin D3 significantly hasten sputum culture conversion in patients with the *tt* genotype of the *Taq*I vitamin D receptor polymorphism [24]. However, C Wejse et al. [12] reported that supplementation of three doses of 2.5 mg vitamin D3 at baseline, 5 months, and 8 months did not influence clinical severity score or time to sputum smear conversion in 365 patients in Guinea Bissau. It is possible that the dose used was insufficient. In our trial, we are supplementing VD by daily dose of 2000 IU cholecalciferol, and we are measuring the effect of the supplementation on clinical treatment in active TB patients with diabetes. In addition, prior studies have found that supplementation of VA or VD is associated with improved β cell function or hasten sputum culture conversion, our trial will allow us to determine whether this association will remain true for VA and/or VD use in patients with both TB and DM who have more severe clinical symptom and poorer prognosis, and the underlying mechanism is being investigated.

Despite its strengths, trial limitations should be noted. In our trial, only some doses of VA and VD are observed. However, we designed these doses on the basis of acquiring important information including the VA nutrition status in China by national survey [25], the recommended VA and VD intake formulated by the Chinese nutrition society. Also, abundant literature researches concerning the VA, VD level in the supplementation trials have been implemented. In addition, different distribution of some aspects of the subject in the four arms such as severity of the disease, fundamental nutrition status, socioeconomics status etc. may interfere or reduce our measured effect size. To minimize the differential effect between the four arms, we balanced the four arms regarding age, sex and randomized the subjects to different groups. Furthermore, multivariate logistic regression will be used to identify the measured size to adjust the possible impact factors.

We expect that results of our VA and/or VD supplementation trial will advance our knowledge of the efficacy of directly observed therapy for active PTB and DM. If our results provide evidence that VA and/or VD supplementation is effective in PTB and DM, further research protocols can be developed to observe the efficacy of other kind of micronutrients related to glucose metabolism and/or anti-mycobacterium on the patient with both PTB and DM. Data from this study will also allow us to examine the optimal biomarkers associated with PTB and DM treatment influenced by micronutrients. Newer regimens for PTB and DM treatment will emerge which may improve outcomes of clinical therapy and/or shorten the treatment period.

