## Methods/design

### Study setting

The VA/D supplementation trial is being conducted in a network of 4 TB clinics in Qingdao and Linyi city in Shandong province in China. Together, these clinics provide care for approximately 5,000 active pulmonary tuberculosis patients per year and nearly 10% have DM. These four clinics are the sites for study recruitment, delivery of the VA and/or VD intervention, and all research visits.

VA and/or VD supplementation is delivered by the physicians, together with the nurses, social workers to take care of the patients. The medical team provides comprehensive medical care, including TB and DM pharmacotherapy.

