### Randomization

Random-number tables are used to allocate subjects to the VA intervention arm, VD arm, VAD arm or the placebo control arm.

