### Planned statistical analyses

We hypothesize that effect of anti-TB and DM treatment in VA and/or VD arms will be better than the effect in the control arm. Descriptive statistics will be calculated and checked for balance in each arm in demographic, physical and other related measurements at baseline. Comparisons among the groups of pulmonary pathological damage, CD_4_^+^ T cell, HOMA-IR, etc., will be performed by Chi-square (categorical variables), F test (continuous variables, normal distribution) or Kruskal–Wallis H test (ranked data). Linear mixed-effects models will be used to analyze the main influencing factors.

We will also calculate anti-tuberculosis and diabetes treatment results, nutritional and immunologic indexes at three time points: before the supplementation (at the inclusion), 2 months after the supplementation, and at the end of the trial (6 to 8 months after the supplementation).

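### Allocation is described as random-number tables in Methods and as balanced on age and sex in the Discussion; the two are not reconciled, and the named between-arm tests carry neither factor.

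*Protocol article*

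**What the plan says.** All statements are in the protocol article.

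- **Randomization** consists of one sentence: "Random-number tables are used to allocate subjects to the VA intervention arm, VD arm, VAD arm or the placebo control arm". It mentions no strata, blocks or minimisation.
- **Discussion**, limitations paragraph: the authors concede that the arms may differ in disease severity, nutrition and socioeconomic status, and that this could distort or reduce the measured effect. Their answer is that "we balanced the four arms regarding age, sex and randomized the subjects to different groups". The next sentence adds that "multivariate logistic regression will be used to identify the measured size to adjust the possible impact factors".
- **Planned statistical analyses**: baseline balance is to be examined ("Descriptive statistics will be calculated and checked for balance in each arm in demographic, physical and other related measurements at baseline"). Between-arm comparisons "will be performed by Chi-square (categorical variables), F test (continuous variables, normal distribution) or Kruskal–Wallis H test (ranked data"). The section then says "Linear mixed-effects models will be used to analyze the main influencing factors". No covariates are named for either model.
- **Study setting**: four clinics in two cities take part. "These four clinics are the sites for study recruitment, delivery of the VA and/or VD intervention, and all research visits".
- **Study sample characteristics**: of the first 37 patients, "8 were randomized to the VA arm, 10 to VD arm, 9 to VAD arm and 10 to the control arm".

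**The concern.** Balancing arms on age and sex is a property of the allocation scheme. It needs a restriction such as strata, blocks within strata or minimisation. The Methods describe none, yet the Discussion relies on one as a safeguard. A reader cannot tell which of two situations applies:

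1. A restricted scheme is in use, and the Randomization section leaves out its defining feature.
2. No restriction is in use, and the Discussion claims a protection the trial does not have.

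The answer bears on the analysis. Under a restricted scheme, variation due to age and sex is largely removed from the between-arm difference. A test without those factors still counts that variation as noise, so its standard error is too large. Without restriction the unadjusted tests have their nominal size, but the balance claim should go.

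**Working it through.** **Step 1. The two allocation statements side by side.** Randomization gives a source of random numbers. The Discussion gives a result, balance on age and sex. Neither section refers to the other, and no section supplies the mechanism that would join them. They can be joined, for example by a list stratified by age group and sex and drawn from a table. They are therefore unreconciled rather than contradictory.

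**Step 2. What the arm sizes so far suggest.** The split of the first 37 patients is 8, 10, 9 and 10, a spread of 10 − 8 = 2. Under simple 1:1:1:1 randomization the counts are multinomial(37; ¼, ¼, ¼, ¼). With 37 patients, only the patterns {8, 9, 10, 10} and {9, 9, 9, 10} give a spread of 2 or less. Summing 37!/(a! b! c! d!) × (¼)^37 over all orderings gives P(spread ≤ 2) = 0.062; the median spread is 6. The totals are closer than unrestricted numbers usually give. This hints at some restriction but does not prove it, and it says nothing about balance on age or sex.

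**Step 3. Cost of leaving the balancing factors out.** The plan has no figure of its own to reproduce here. Assumptions: a continuous outcome; a comparison of two arms; allocation perfectly balanced on factors that explain a fraction R² of outcome variance; a nominal two-sided 5% test with 90% power at R² = 0 (90% is the article's stated power). R² is assumed, since the article gives nothing from which to estimate it.

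The true standard error of the difference is proportional to √(1 − R²), while the unadjusted test uses 1. Hence:

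- Interval widening, unadjusted against adjusted: 1/√(1 − R²) − 1.
- Actual size of the unadjusted test: 2[1 − Φ(1.960/√(1 − R²))].
- Power, unadjusted: Φ(1.282/√(1 − R²)).
- Power, adjusted: Φ((1.960 + 1.282)/√(1 − R²) − 1.960).

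| R² (assumed) | √(1 − R²) | Interval widening | Actual size | Power, unadjusted | Power, adjusted |
|---|---|---|---|---|---|
| 0.05 | 0.975 | 2.6% | 0.044 | 0.906 | 0.914 |
| 0.10 | 0.949 | 5.4% | 0.039 | 0.912 | 0.927 |
| 0.15 | 0.922 | 8.5% | 0.034 | 0.918 | 0.940 |

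For R² = 0.05, for example: 1/0.9747 − 1 = 0.026, and 2[1 − Φ(2.011)] = 0.044. Size stays below 5% throughout.

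**Step 4. How much sex balancing could contribute.** Table 1 shows 3 women among 37 (8.1%). At that rate 400 patients would include about 0.081 × 400 ≈ 32 women, or 8 per arm. Sex can explain little variance in such a sample, so any sizeable R² would have to come mainly from age.

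**The case against.** **The statements can both be true.** The Randomization section does not say that allocation is simple or unrestricted, and a table can generate a stratified or blocked list. This stands, and it is why the point is a failure to reconcile and not a proven contradiction.

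**Adjusted analyses are already planned.** The sentence after the balance claim plans a logistic regression with adjustment, and the analysis section plans mixed models. This also stands: it would be wrong to say the plan has no adjusted analysis. What remains is that the tests named for between-arm comparison are unadjusted, and neither model is linked to the two factors on which the arms are said to be balanced.

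**An article condenses.** Silence on stratification by clinic, on who holds the list and on full covariate lists may be filled by a document not shown. That is fair, and none of those silences is counted here as an error. It does not cover two positive statements about the same procedure that do not match.

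**The size is small and rests on an assumed R².** True. The formula is also for continuous outcomes and does not carry over directly to the categorical ones, which go to chi-square and logistic regression.

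**Stronger readings that the document does not support.** A reader might infer that staff balance the arms by hand from a visible table, so that the next assignment can be foreseen. Nothing says so: no section states who holds the table, and the Baseline assessment section places assignment after the baseline assessment is complete. A reader might also infer that clinic was deliberately left out; the article simply does not mention it. Nor does the 0.062 establish that a restricted scheme is in use.

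**Conclusion.** The point holds in limited form. The article describes allocation in two ways that it does not reconcile, and it relies on one of them as a safeguard against a limitation it concedes. If allocation is restricted on age and sex, the named chi-square, F and Kruskal–Wallis tests are slightly conservative. Intervals for a continuous outcome are about 3% to 8% wider than adjusted ones, and power is lower by about 0.01 to 0.02 (0.906 against 0.914; 0.918 against 0.940). This rests on an assumed R² of 5% to 15% and on near-perfect balance. There is no type I error inflation. If there was no restriction, those tests keep their nominal size and the fault lies in the balance claim alone. A defective allocation scheme or predictable assignment is not shown. The change is worth making because it is nearly free and recruitment is at an early stage.

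**What to change.** 1. Reconcile the Randomization section and the Discussion by stating the method actually used, including how age and sex were balanced. If no restriction was used, delete the balance claim.
2. Make the primary between-arm comparison the regression or mixed model already planned, with arm as the factor of interest and age, sex and clinic as prespecified covariates. Clinic is known for every patient, so including it needs no new data. Keep the chi-square, F and Kruskal–Wallis tests as supportive.
3. Optional, as good practice and not as correction of a shown error: for the remaining 400 − 37 = 363 patients, use a concealed, pre-generated list in permuted blocks stratified by clinic. If the method changes, add allocation period as a covariate.

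Items 1 and 2 cost a few sentences and need no extra patients, visits or data. Item 3 costs a new list and its administration.

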## Abbreviations

PTB: Pulmonary tuberculosis;DM: Diabetes mellitus;VA: Vitamin A;VD: Vitamin D
